**Exclusion criteria for healthy volunteers MRI scans and patients optional MRI scans:**

- Contraindications for MRI scanning: having pacemakers, defibrillators, neurostimulators, prohibited medical implants, and foreign bodies (e.g. bullets, shrapnel, metal slivers), history of metallic foreign body in eye(s) and penetrating eye injury that could present a risk during an MRI scan.
- Difficulty breathing or inability to lie flat, as well as conditions that could worsen under stress (such as anxiety or panic disorders, claustrophobia, uncontrolled hypertension, or seizure disorders) severe enough to prevent undergoing an MRI.
- Contraindications to Hyoscine butylbromide (Buscopan®): Previous adverse drug reaction (allergic, hypersensitivity or other), Angle-closure glaucoma, tachycardia, ischaemic heart disease, myasthenia gravis, prostatic enlargement with urinary retention requiring catheterisation, mechanical stenosis in the gastrointestinal tract, paralytic or obstructive ileus, hypotension, cardiac disease, recent heart attack or any arrhythmias, thyrotoxicosis, gastro-oesophageal reflux disease, hiatus hernia, ulcerative colitis.

### Expected duration of participant participation

### Study participants will be participating in the study for 6 weeks, attending two 2 hours study visits. Participants who will agree to have MRI scans, including healthy volunteers, will need to attend two 4 hours MRI visits.

### Removal of participants from therapy or assessments/Participant Withdrawal

Participants may be withdrawn from the trial either at their own request or at the discretion of the Investigator due to safety reasons (including pregnancy) or development of severe adverse events, or due to failure to adhere to protocol requirements. The participants will be made aware that this will not affect their future care. Participants will be made aware (via the information sheet and consent form) that should they withdraw the data collected to date cannot be erased and may still be used in the final analysis. The research team will advise pregnant participants to stop the intervention and contact their GP if they have questions.

Study team will try their best to replace withdrawn participants.

### Informed consent

All study participants will provide written informed consent to a consent-trained researcher that will be taken in person at Nottingham University Hospitals NHS Trust during the screening visit.

Similarly, all healthy volunteers will provide written informed consent to a consent-trained researcher that will be taken in person at Sir Peter Mansfield Imaging Centre (SPMIC).

The Informed Consent Form will be signed and dated by the participant before they enter the trial. The researcher will explain the details of the trial and provide a Participant Information Sheet, ensuring that the participant has sufficient time to consider participating or not. The researcher will answer any questions that the participant has concerning study participation.

Informed consent will be collected from each participant before they undergo any interventions (including physical examination and history taking) related to the study. One copy of this will be kept by the participant, one will be kept by the researcher, and a third will be retained in the patient’s hospital records.

Should there be any subsequent amendment to the final protocol, which might affect a participant’s participation in the trial, continuing consent will be obtained using an amended Consent form which will be signed by the participant.

# TRIAL / STUDY INTERVENTION AND REGIMEN

Interested participants will be asked to contact the study team using the provided contact details on the advertisement poster or the study team will directly contact the potential participants if they are referred for recruitment by patient’s usual care team (which may include the investigator)at hepatology clinic via using encrypted emails (consent to share contact details will be documented in the patients notes) or those who have consented to contact for future research. The Participant Information Sheet (PIS) will be given to those expressing interest, either in person at NIHR Nottingham Clinical Research Facility at Nottingham University Hospitals NHS Trust, Queens Medical Centre or via royal mail or email. Study team contact information will be included in the PIS. Participants will have up to one week to decide whether they wish to take part or not. If a participant expresses interest after reading the PIS, they will be invited for a screening visit, which will be conducted in the NIHR Nottingham Clinical Research Facility at Nottingham University Hospitals NHS Trust, Queens Medical Centre by a trained member of the study team. During screening visit, the research team member will go through study details, allow the participant to ask any questions they have, and consider their decision. If they are willing to participate, they will be asked to provide consent and will be formally enrolled in the study. The research team member or member of the usual care team will then go through eligibility checklist with the participant to confirm their eligibility to participate in the study. If the medical notes are not available for participants to check their eligibility, then the chief investigator will rely on participants answers regarding their medications and medical conditions to confirm eligibility. A trained research Practitioner or nurse, who will be a member of research team at Nottingham University Hospital NHS Trust, will also perform CAP- FibroScan™ to measure liver fat and stiffness (if not completed in past month or not available in the medical note) and the result will be provided to the participant at the visit and will be documented in the medical notes. FibroScan™ results will be sent to the chief investigator to confirm eligibility.

FibroScan ™ is owned and maintained by Nottingham University Hospitals NHS Trust.

If chief investigator finds anything abnormal on FibroScan™ results, the investigator will arrange for an appropriately qualified doctor, from a healthcare provider e.g. a NHS Trust or a private doctor, to look at them. That specialist doctor would contact participants GP to explain the situation, so that GP could then advise the participant.

Due to FibroScan™ requirements, participants will be asked to stop eating 4 hours before the scan visit, stop drinking alcohol 24 hours before the scan visit and to stop drinking water 2 hours prior to the scan visit.

Research team will schedule an onsite baseline visit with eligible participant. Participants will be given a stool collection kit before scheduling their baseline visit. Stool kit will be given either in person or mailed to the participant.

If participant gave consent and were found not to be eligible, including FibroScan™ results, then the study team will not enrol them within the study.

All in person visits will be conducted at adult NIHR Nottingham Clinical Research Facility at Nottingham University Hospitals NHS Trust, Queens Medical Centre or at Sir Peter Mansfield Imaging Centre (SPMIC).

**Screening and recruitment flow diagram:**

**Hepatology Clinics/ Posters/email/**

**social media/ phone calls**

**Provide PIS**

**(visit/ email)/ provide invitation letter with PIS to referred patient (visit/ email)**

**Participant Consented and screened**

**Recruited into study**

*Invitation*

*Screening*

*Enrolment*

Contact study team/ referred to study team

Eligible participants

**Baseline measures (visit 1):**

Participants will attend the visit fasted for at least 6 hours and provide the stool samples. Anthropometric measurements, including weight, height, waist/hip ratio and blood pressure, will be taken in duplicate by a trained researcher using standard procedures. A trained researcher will collect a blood sample (not more than 40ml) for analysis. Moreover, if participants consent to genetic testing, then blood sample for genetic analysis will be taken too. After randomisation, participants will receive their assigned pre-weighed supplement in food-grade pouches.

All the research activities at baseline visit will be done by [name] except blood and stool samples collection that will be done by a trained research practitioner or nurse, who will be a member of research team at Nottingham University Hospital NHS Trust.

**MRI visit 1 and 2:**

If the participant consents to have MRI scans, then the study team will schedule a scan for them within the same day of baseline visit. Both MRI scans visits will be arranged at the Sir Peter Mansfield Imaging Centre (SPMIC). The participant will attend the visit fasted and provide the stool sample. The MRI research team will use Philips 3T MRI scanner. The team will firstly scan the hepatic fat and other surrounding GI organs fat using Dixon MRI sequences. Then, a medical doctor will cannulate the participant, take a blood sample from the participant and will ask them to drink the oral contrast which consists of 2.5% Mannitol and 0.2% Locust Bean Gum and will be prepared at the SPMIC on the morning of the scan. The participant will be asked to drink the oral contrast gradually over 40 minutes. This contrast required to provide contrast between the lining of the gut and its contents. After that, the medical doctor will prescribe and administer hyoscine butylbromide (Buscopan®) through the cannula while MRI research team taking T2* MRI measures of gut wall to measure gut permeability. Buscopan® is used to stop the bowel moving to allow the team to generate clear pictures of the bowel wall.

The medical doctor will confirm eligibility and document this, prior to performing any research activity related to the cannulation/administration of hyoscine butylbromide (Buscopan®).

Both MRI and baseline visit will take around 4 hours to complete all the research activities.

It is extremely unlikely that MRI scan will show any abnormality. Even if there were an abnormality, it is unlikely that research team would notice it since we are taking these MRI scans for scientific research, so they are not the same as scans collected by doctors for medical purposes. Furthermore, the pictures will not be looked at by a radiologist.

If the research team did find anything abnormal on the MRI scan, the investigator would arrange for an appropriately qualified doctor, from a healthcare provider e.g. a NHS Trust or a private doctor, to look at them. That specialist doctor would contact participant GP to explain the situation, so that participant GP could then advise them.

**Dietary intervention (6 weeks):**

Control and intervention arms: Each participant will be randomly assigned to either pectin with whey protein and cocoa powder or control whey protein with cocoa powder using online software (sealedenvelope.com) to determine intervention A or B at enrolment. Randomisation will ensure equal distribution of key characteristics that might confound between-group comparisons and will be evaluated using baseline data analysis. Participants in the intervention arm (N=15) will be required to take 15g of pectin combined with 15g of unflavoured whey protein powder and 5g of cocoa powder as a flavour per day for a period of 6 weeks. The participants in the placebo/control arm (N=15) will be required to take 30g of unflavoured whey protein powder combined with 5g of cocoa powder as a flavour per day for the same period of 6 weeks. All supplements will be provided, pre-weighed, in food grade pouches and will be given sufficient cover the total intake for the 6-weeks period. Participants will be asked to incorporate the supplement provided in 250-300ml of water taken once at morning or evening. Regular weekly contact will be made via phone calls by [name] to record patients’ feedback or any adverse event that might occur due to ingestion of supplements and to ensure participants receive any information that becomes available during the course of the research that may be relevant to their continued participation .

**Follow-up/end of study measures (visit 2)**

At the end of 6 weeks, as for visit 1, stool samples and fasting blood samples (not more than 40ml), including blood sample for genetic analysis if the participants consented to that, will be collected, weight, height, waist/hip ratio and blood pressure measured, and FibroScan™ performed. The last visit will last no longer than 2 hours.

All the research activities at follow-up visit will be done by [name] except blood and stool samples collection and FibroScan™ that will be done by a trained research practitioner or nurse, who will be a member of research team at Nottingham University Hospital NHS Trust.

If the participant agrees to have MRI scans, then the study team will schedule a follow-up MRI scan as for MRI visit 1, taking around 4 hours.

**Schedule of events**

|  | Screening | Visit 1 Baseline visit  (Day 1) | Visit 2 (6 weeks after visit 1) |
| --- | --- | --- | --- |
| Assessing participants eligibility and informed consent | X |  |  |
| Fasting blood sample collection |  | X | x |
| Faecal sample (collection by participant at home & brought to visit) |  | X | x |
| Anthropometric measurements (weight, height, waist/hip ratio and blood pressure) |  | X | x |
| CRF completion (demographics, health/med history) |  | x | x |
| Randomisation |  | X |  |
| Dietary supplementation Intervention start (dispense supplements and instruct) |  | x |  |
| FibroScan™ | x |  | x |
| MRI screening questionnaire (optional) |  | x | x |
| MRI (optional) |  | x | x |

**Healthy Volunteers MRI Scans**

Both healthy volunteers MRI scans visits will be arranged at the Sir Peter Mansfield Imaging Centre (SPMIC). The participant will attend the visit fasted. The MRI research team will use Philips 3T MRI scanner. The team will firstly scan the hepatic fat and other surrounding GI organs fat using Dixon MRI sequences. Then, a medical doctor, who is a member of the University of Nottingham research ream, will cannulate the participant, take a blood sample from the participant and will ask them to drink the oral contrast which consists of 2.5% Mannitol and 0.2% Locust Bean Gum and will be prepared by MRI research team at the SPMIC on the morning of the scan. The participant will be asked to drink the oral contrast gradually over 40 minutes. This contrast required to provide contrast between the lining of the gut and its contents. After that, the medical doctor will prescribe and administer hyoscine butylbromide (Buscopan®) through the cannula while MRI research team taking T2* MRI measures of gut wall to measure gut permeability. Buscopan® is used to stop the bowel moving to allow the team to generate clear pictures of the bowel wall.

The medical doctor will confirm eligibility and document this, prior to performing any research activity related to the cannulation/administration of hyoscine butylbromide (Buscopan®).

Each MRI scans visit will take around 4 hours.

It is extremely unlikely that MRI scan will show any abnormality. Even if there were an abnormality, it is unlikely that research team would notice it since we are taking these MRI scans for scientific research, so they are not the same as scans collected by doctors for medical purposes. Furthermore, the pictures will not be looked at by a radiologist.

If the research team did find anything abnormal on the MRI scan, the investigator would arrange for an appropriately qualified doctor, from a healthcare provider e.g. a NHS Trust or a private doctor, to look at them. That specialist doctor would contact participant GP to explain the situation, so that participant GP could then advise them.

### Compliance

No interim data analyses are planned and given the simplicity of the study we will not need a data monitoring committee nor the overview of a formal study steering committee. The participant’s involvement in the study will only be terminated if the participant wishes to do so or if participants or caring clinician feel that the participants are too unwell to carry on with the study.

The study will be terminated if the participant safety is deemed to be at risk throughout the study.

### Criteria for terminating trial

Stopping the trial is unexpected however might be considered if a major safety concern will be reported or due to poor recruitment or loss of resources. In such case, unused supplements stock will be disposed as food waste into landfill waste.

Research data will be archived based on the archiving plan.

## TRANSPORT AND STORAGE OF THE TISSUES

Samples will be stored in a linked anonymised format and labelled using a combination of study reference, unique study identifier and cross referenced with location code numbers to permit accurate linkage to study data and the consent form. Where participant’s consent, samples will be collected for analysis of common genetic variants associated with development of gut permeability [15].

Stool samples will be collected and stored in aliquots at -80°C.

Blood samples will be collected and either sent for clinical analyses or stored or processed to obtain plasma and serum aliquots which will be stored at -80°C. They will be transported within the building from the patient to the lab in double containment with absorbent material and following Biosafety requirements.

The master sample database will be held by the research team in a password encrypted file.

The analysis of samples will take place at the University of Nottingham within the School of Medicine located in the Queens Medical Centre, or at Nottingham University Hospitals NHS Trust, Queens Medical Centre clinical laboratories or at contracted commercial service providers.

Samples will be transferred by an approved courier for analysis by external agents at the end of the study. All shipments will contain a complete inventory of all samples, along with the name of the person responsible for sending the samples. Any remaining samples at the University of Nottingham will be stored either under the University HTA Licence (DI [name]- Licence Number 12265) or within a Research Tissue Bank for future research if participants are agreeable and sign the optional clause on the consent form.

Where participants do not agree to the future use of the samples they will be destroyed after the study ends in accordance with the Human Tissue Act, 2004.

## LABORATORY ANALYSES

Microbial DNA will be extracted from stool samples by the research laboratory team and sent for specialist sequencing analysis to obtain the corresponding DNA sequences. From this we can determine the bacterial species present based on their characteristic DNA signatures.

Blood biomarkers and metabolites will be analysed by the research laboratory team using commercial assay kits or sent for specialist analytics by contracted commercial laboratories. Genetic variants such as MUC2 will be determined where consent for genetic analysis is given.

The laboratory work by the research team will take place in the School of Medicine Labs in the Queens Medical Centre which are centrally managed. All equipment is appropriately calibrated, maintained and serviced.

# STATISTICS

### Methods

The data will be analysed by [name] on-site at the University of Nottingham under supervision of the CI, co-investigators and NIHR Nottingham Biomedical Research Centre liver/GI statistical team.

All analyses will be conducted on password-protected University of Nottingham computers or University of Nottingham laptops, that are backed up to cloud servers.

Data input, cleaning and analysis will be conducted using a statistical software such as PRISM or SPSS (IBM Corp, Armonk, New York) or R software (R Foundation for Statistical Computing, Vienna, Austria). Descriptive statistics will be reported as means ± standard deviations (SD) or medians with interquartile ranges (IQR) for continuous variables, and as frequencies and percentages for categorical variables. Prior to analysis, data will be checked for normality using the Shapiro-Wilk test. Standard parametric and non-parametric tests (where assumptions of normality are violated) will be used to assess significance of changes compared to baseline Characteristics of participants, outcome measures at baseline (symptoms, clinical parameters) and post-intervention will be summarized by intervention group using descriptive statistics. The differences between the two groups will be tested by matched-pair Student’s t-test. Data will be presented as mean± standard deviation and the significance of difference will be set at p <0.05.

Mixed-effects linear regression models will be used to assess the intervention effect of pectin compared to placebo, adjusting for baseline values and relevant covariates such as age, sex, ethnicity and BMI. The interaction between time (baseline and follow-up) and group (pectin vs placebo) will be examined to determine if the changes over time differ between the two groups.

Any changes in the planned statistical methods will be documented in the study report.

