| Statistical methods | Data input, cleaning and analysis will be conducted using a statistical software such as PRISM or SPSS (IBM Corp, Armonk, New York) or R software (R Foundation for Statistical Computing, Vienna, Austria). Descriptive statistics will be reported as means ± standard deviations (SD) or medians with interquartile ranges (IQR) for continuous variables, and as frequencies and percentages for categorical variables. Prior to analysis, data will be checked for normality using the Shapiro-Wilk test. Standard parametric and non-parametric tests (where assumptions of normality are violated) will be used to assess significance of changes compared to baseline on both pectin arm and placebo arm. Mixed-effects linear regression models will be used to assess the intervention effect of pectin compared to placebo, adjusting for baseline values and relevant covariates such as age, sex, ethnicity and BMI. The interaction between time (baseline and follow-up) and group (pectin vs placebo) will be examined to determine if the changes over time differ between the two groups. P-value < 0.05 will be considered statistically significant for all analyses. |

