## RANDOMIZATION AND BLINDING

The study will be a parallel design, placebo controlled, randomised intervention study in which participants will be allocated to either the intervention or placebo arm. The randomisation will be done through an online software (sealedenvelope.com) to determine intervention A or B at enrolment.

One of research team will be un-blinded and will be responsible for preparing and labelling of the intervention/placebo as either A or B based on random selection using an online software (sealedenvelope.com). A or B – pectin will be assigned to the arm in the first envelope. This information will be securely documented in a new sealed enveloped stored in the chief investigators locked desk. All other members of the team will be blinded to the assignment of A or B as the intervention.

This will be unblinded once the study is complete after the sample analysis and data analysis is complete.

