### Secondary endpoint

- Change in BMI
- Change in general metabolic indicators such as fasting blood glucose
- Changes in blood-based markers relevant to MASLD (e.g., CK18-M30, CK18-M65, PROC3, Enhanced Liver Fibrosis (ELF), NIS2+™, YKL-40, microRNA miR-34a-5p, liver-associated enzymes such as Alanine Aminotransferase (ALT), Aspartate Aminotransferase (AST), gamma-glutamyl transferase (GGT), Alkaline Phosphatase (ALP)), bilirubin levels, lipid profiles, and platelet counts.
- Gut microbiome: changes in composition
- Change in non-invasive physiological assessments linked to liver characteristics: FibroScan™ CAP value and Liver stiffness based on vibration-controlled transient elastography (VCTE)
- Change in liver fat and other surrounding abdominal organs fat through alterations in Dixon MRI sequence
- Alterations in T2* MRI measures of intestinal permeability

The efficacy parameters for the primary and secondary endpoints will involve calculating the difference between baseline visit and follow-up visit in both study arms and compare between two arms. Moreover, they will be used in calculating correlation coefficients (Pearson's or other appropriate methods) between the effect of pectin compared to placebo, adjusting for baseline values and relevant covariates such as age, sex, ethnicity and BMI. These correlation coefficients will indicate the strength and direction of the relationships between the variables.

Primary endpoint has been identified based on the results on a recent study that was conducted at University of Nottingham, showed that 4 weeks ingestion of 15-20g/day of LM pectin in healthy volunteers significantly reduced pro-inflammatory blood markers [31].

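### The Methods section names a matched-pair t-test for comparing two unpaired parallel arms, beside a usable mixed model, and does not say which analysis decides efficacy

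*Protocol*

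**What the plan says.** Under Randomization and Blinding, the protocol says: "The study will be a parallel design, placebo controlled, randomised intervention study in which participants will be allocated to either the intervention or placebo arm". It describes no crossover and no matching of one participant to another.

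The Methods section of Statistics then refers to the arms in three ways:

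- Parametric or non-parametric tests "will be used to assess significance of changes compared to baseline". The synopsis adds that these are done in each arm: "assess significance of changes compared to baseline on both pectin arm and placebo arm".
- "The differences between the two groups will be tested by matched-pair" Student's t-test, with significance at p < 0.05. The synopsis does not contain this sentence.
- "Mixed-effects linear regression models will be used to assess the intervention effect of pectin compared to placebo", adjusted for baseline and for covariates such as age, sex, ethnicity and BMI. In addition, "The interaction between time (baseline and follow-up) and group (pectin vs placebo) will be examined". The synopsis says the same.

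Assessment of Efficacy adds, for the primary and secondary endpoints, "calculating the difference between baseline visit and follow-up visit in both study arms and compare between two arms", without naming a test. None of these analyses is designated as the one that decides efficacy.

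**The concern.** A paired t-test needs a natural link between each observation in one group and one observation in the other. This design has no such link between arms. The analyst would have to create one, for instance from row order, and the p-value would then depend on that choice.

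If the pairing was meant to be baseline against follow-up in the same person, the test is legitimate. It then tests change within an arm, not the difference between arms that the sentence announces.

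The primary endpoint therefore has two between-arm methods that can disagree, and one of them does not fit the design. Within-arm tests against baseline stand next to them. Those tests do not estimate the randomised effect, and the text does not say that they carry no weight as evidence for pectin.

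**Working it through.** **Inputs.** From the protocol: 15 per arm, two arms, significance level 0.05. Assumed, because the protocol does not give them: a two-sided test, a between-arm effect of 0.8 SD (1.0 SD as a second case), and for the within-arm check a common change of 0.5 SD of the change score. The protocol states no power for either test, so there is no figure of its own to reproduce.

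**Why the pairing matters.** The paired statistic is t = (mean difference) / √[(s_A² + s_B² − 2·r·s_A·s_B)/n], where r is the sample correlation across the chosen pairs. The mean difference does not depend on the pairing, but r does. Take equal SDs of 1 and a data set that sits exactly at independent-samples p = 0.050, so that the mean difference is 2.048 × √(2/15). The paired statistic then reduces to 2.048/√(1 − r) on 14 df:

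| r produced by the pairing | t | p (14 df) |
|---|---|---|
| +0.5 | 2.897 | 0.012 |
| 0 | 2.048 | 0.060 |
| −0.5 | 1.673 | 0.117 |

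In one simulated data set of this kind, 20,000 random re-pairings gave a central 95% range for p of 0.012 to 0.119, and 39% of the pairings fell below 0.05.

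**How often the verdict is affected, at a true effect of 0.8 SD.** In about a third of simulated trials (32%), each verdict appears in more than 5% of the possible pairings. In 51%, at least one of 300 pairings changes the verdict. For a single random pairing, the verdict differs from the independent-samples test in about 8% to 9% of trials.

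**Degrees of freedom and power.** Independent test: 15 + 15 − 2 = 28 df, critical t 2.048. Paired test: 15 − 1 = 14 df, critical t 2.145. With arbitrary pairs both have noncentrality d·√(n/2).

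- d = 0.8: noncentrality 0.8 × √7.5 = 2.19; power 56.2% independent, 53.2% paired.
- d = 1.0: noncentrality 2.74; power 75.3% independent, 72.2% paired.

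**Type I error.** In 40,000 simulated null trials it was 4.94% for the independent test and 4.97% for the arbitrarily paired test. Pairing by rank on the outcome gave 55%, but nothing in the protocol suggests that.

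**Unequal arms.** The withdrawal section promises only an attempt at replacement. As an illustration, with 15 and 13 completers the paired test uses 13 pairs (12 df) and drops two people. The independent test keeps all 28 (26 df).

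**Within-arm tests.** Suppose both arms change by the same 0.5 SD, so that there is no pectin effect. Each within-arm test has noncentrality 0.5 × √15 = 1.94 on 14 df and is significant with probability 0.438. Exactly one arm is then significant with probability 2 × 0.438 × 0.562 = 49%, and pectin alone in 25%. If neither arm changes, the figures are 2 × 0.05 × 0.95 = 9.5% and 4.75%.

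**The case against.** The strongest reply is that the protocol already plans a sound comparison. The paragraph after the matched-pair sentence assigns the pectin-versus-placebo effect to a baseline-adjusted mixed model, the synopsis repeats this without the matched-pair test, and Assessment of Efficacy plans to compare changes between arms. The sentence also follows visibly spliced text, so it may be a drafting slip for a before-and-after test. This stands. A reader might infer that the trial's efficacy claim would rest on an arbitrary p-value, but the documents do not support that, because a usable between-arm model is named for the same purpose.

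A reader might also infer that the paired test produces false positives. It does not when the pairing is truly arbitrary, and the power loss is about three percentage points. The wide swings in p apply to results near the threshold.

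On the within-arm tests, the protocol nowhere says that efficacy will be claimed from significance in one arm and not in the other. The 49% depends on an assumed common change, and removing every within-arm p-value would be partly a reporting preference.

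The reply does not remove the error. The sentence expressly assigns the test to the between-group difference, and nothing in the protocol ranks it below the mixed model.

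**Conclusion.** Wrong as written. A matched-pair t-test is inapplicable to two independent parallel arms, because its result depends on an arbitrary pairing, it halves the degrees of freedom and it discards data when the arms are unequal.

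The numerical damage is modest. Type I error stays near 5% under arbitrary pairing, power falls from 56.2% to 53.2%, and one random pairing disagrees with the correct unpaired test in about 8% to 9% of trials. These figures assume 15 per arm and two-sided testing. The power and disagreement figures also assume a true effect of 0.8 SD, and other effect sizes would change them.

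The weightier problem is that the inapplicable test and a usable model serve the same endpoint and the protocol does not say which decides. The within-arm tests are secondary: they need a label that limits their use.

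**What to change.** In the Methods section of Statistics, delete the matched-pair t-test as a between-group test. If an unadjusted check is wanted, name an independent-samples Welch t-test.

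In that section and in the synopsis, state that efficacy is judged by the baseline-adjusted difference between arms at week 6, with a 95% CI. The mixed model already planned can provide this. State also that changes from baseline within each arm are descriptive or supportive and are not evidence of a pectin effect.

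The cost is a few sentences in two places, with no extra participants, visits or assays. Make the change before any arm comparison is run.
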